### Criteria for discontinuing or modifying allocated interventions {11b}

Patients who could no longer use the wristband because of an adverse effect will stop the treatment. However, they will be followed in the study until the end of their participation. In case of a serious adverse event that no longer allows the patient to participate in the study, the patient’s participation will be stopped. The reason for any discontinuation of treatment or study will be documented and recorded.

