### Outcomes {12}

The primary outcome is to compare between the two randomization groups the percentage of patients who significantly improve their fibromyalgia-specific quality of life between the inclusion visit at D0 and the 3-month visit (M3). The fibromyalgia-specific quality of life is evaluated with the French-validated version of the self-questionnaire Fibromyalgia Impact Questionnaire (FIQ). A decrease in FIQ score of 14% or more is considered clinically meaningful [29].

In secondary outcomes number 1 to 5, we compared between the two groups the evolution from D0 to M3 of criteria related to the symptoms of fibromyalgia patients:Questionnaires: Quality of sleep on the Pittsburg Sleep Quality Index (PSQI); Anxiety and depression on the Hospital and Anxiety Depression scale (HAD); Fatigue on the Multidimensional Fatigue Inventory questionnaire (MFI 20); General quality of life on the EQ-5D-5L; Physical activity on the Global Physical Activity Questionnaire (GPAC)Average pain score over the week on a visual analogic scale (VAS)Class, dose, and the number of analgesic, antidepressant, and sleeping pill intake. Patient-reported dose and number of these treatments in his home follow-up bookletConsumption of care in relation to the symptoms of fibromyalgia reported each week by the patient in his home follow-up booklet: care (procedures, medical consultations, hospitalizations); complementary care (acupuncture, osteopath, naturopath, etc.); psycho-behavioral therapies; complementary treatments (phytotherapy, homeopathy, food supplements)Number of steps measured by the subject’s smartphone and collected through the Fibrepik mobile application.

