### Sample size {14}

Considering an alpha risk of 5% and a beta risk of 10%, and assumptions of a rate of patients with a clinically relevant decrease in FIQ of 50% in the Immediate solution group, versus 25% in the Delayed solution group, the number of subjects needed for a comparison of proportions is 77 per group (154 in total). Considering a 10% risk of loss to follow-up, the number of 85 patients per group will be retained (170 patients in total). The clinically relevant decline retained is 14% on the FIQ scale [29].

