## Statistical methods

### Statistical methods for primary and secondary outcomes {20a}

Descriptive analyses will be expressed by means − standard deviations and medians − interquartiles for quantitative data, as well as numbers and percentages for qualitative data.

The analysis of the primary endpoint will be performed using a Fisher exact test. For secondary endpoints at M3, all endpoints evaluating a change in score between D0 and M3 will be analyzed via bivariate linear regressions, considering the randomization group and the value of the score at D0. Qualitative criteria will be analyzed using a Fisher test. The secondary endpoint 8 is descriptive and will follow indications for descriptive analysis. For secondary endpoint 9, since analysis considers several measurement points with different states, mixed regressions (linear or logistic depending on the type of variable) will be implemented. Data at M6 from the delayed intervention group will be analyzed for comparison at M3 via a McNemars test (test of proportions for paired data).

These analyses are planned in two stages: (i) all criteria evaluated at 3 months will be performed when all patients have made their follow-up visit at M3 and (ii) all criteria evaluated at 6 and 9 months will be analyzed when the follow-ups at M9 of all patients are completed.

The results will be presented in accordance with the recommendations of the CONSORT Statement. These analyses will be implemented after a consistency check and a freeze of the database, in accordance with the good practices of the Grenoble Alps University Hospital. The software used will be Stata 15 or a more recent version (StataCorp LLC).

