### Methods in analysis to handle protocol non-adherence and any statistical methods to handle missing data {20c}

All analyses will be performed in Intention-To-Treat. In addition to this analysis, a per-protocol analysis will be performed by keeping only patients who have been compliant with the treatment. We consider that a patient is compliant if during the first 3 months of solution use, we observe at least 80% of days with two or more sessions per day. This number of sessions is an extract of the wristband log file.

Missing data within the FIQ questionnaire will be accounted for following the recommendations of the scale authors [38]. A sensitivity analysis of the primary endpoint will be performed by imputing missing data not managed via the FIQ use recommendations via multiple imputation if these missing data represent between 5 and 20% of the total data.

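### The only stated missing-outcome analysis of the primary endpoint is switched off when more than 20% of data are missing, its denominator is unclear, and nothing planned departs from missing at random

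*Protocol article*

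**What the plan says.** In the protocol article:

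- **Population, {20c}:** "All analyses will be performed in Intention-To-Treat".
- **Gaps inside a completed questionnaire, {20c}:** "Missing data within the FIQ questionnaire will be accounted for following the recommendations of the scale authors".
- **What remains missing, {20c}:** "A sensitivity analysis of the primary endpoint will be performed by imputing missing data not managed via the FIQ use recommendations", done "via multiple imputation if these missing data represent between 5 and 20% of the total data". Nothing is stated for less than 5% or more than 20%.
- **Primary test, {20a}:** "The analysis of the primary endpoint will be performed using a Fisher exact test". It is applied to responder status from D0 to M3. On the responder threshold, Outcomes {12} says: "A decrease in FIQ score of 14% or more is considered clinically meaningful".
- **Sample size, {14}:** 77 per group, raised to 85 per group. The reason given is "Considering a 10% risk of loss to follow-up".
- **Blinding, {17a}:** the physician is blinded; the coach and the patient are not.

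The article gives no rule for a patient who has no M3 FIQ, such as counting that patient as a non-responder.

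**The concern.** A check on missing outcomes is needed most when many are missing. This rule works the other way: above 20% the single stated check disappears, while the intention-to-treat label stays.

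Two features make it worse. First, total data could mean patients, FIQ forms, FIQ items or the whole database. Whether the check runs could then depend on a denominator chosen after the data are seen. Second, multiple imputation in its standard form assumes missing at random, and no analysis that relaxes this is stated at any level of missingness. In an unblinded comparison with a waiting group, the reasons for a missing M3 form can differ by arm. If they also relate to response, an observed-case test can produce a difference that dropout explains, with no planned analysis to show it.

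**Working it through.** **1. The plan's own figure.** Inputs from {14}: 50% versus 25%, alpha 5% (taken as two-sided), power 90%. With mean proportion 0.375:

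n = [1.960 × √(2 × 0.375 × 0.625) + 1.2816 × √(0.50 × 0.50 + 0.25 × 0.75)]² / 0.25² = (1.342 + 0.848)² / 0.0625 ≈ 76.7, so 77 per group.

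This matches. For the allowance, 77 × 1.10 = 84.7, so 85 per group, also as stated. Adding patients to replace losses fits a primary test on observed patients.

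**2. The window in patients.** 5% of 170 = 8.5 and 20% of 170 = 34. The check runs at 9 to 34 missing and stops at 35 (35/170 = 20.6%). The planned 10% is 17 patients, inside the window.

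**3. The denominator.** Suppose total data means the D0 and M3 FIQ forms together, 2 × 170 = 340, with D0 complete because it is needed for eligibility and stratification. Then 35 missing M3 forms are 35/340 = 10.3%, and the check runs. Read as patients, the same 35 are 20.6%, and it does not.

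**4. A result just outside the window.** The article gives no split by arm, so 26 Immediate and 9 Delayed missing (35 in all) is an assumption. Observed rates are set near the design values.

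| Handling of missing | Immediate | Delayed | Fisher p |
|---|---|---|---|
| Observed cases | 30/59 (50.8%) | 19/76 (25.0%) | 0.002 |
| Missing = non-responder | 30/85 (35.3%) | 19/85 (22.4%) | 0.09 |

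**5. False-positive rate of the observed-case test.** Assume a true response of 25% in both arms and that every missing patient is a non-responder. Expected responders are 0.25 × 85 = 21.25 per arm, so the observed-case rate is 21.25/(85 − missing). Rejection at two-sided 5% comes from exact enumeration of the Fisher test with binomial counts at those rates.

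| Missing, Immediate / Delayed | Overall | Observed-case rates | Rejection |
|---|---|---|---|
| 17 / 17 | 20.0% | 31.3% / 31.3% | 3.4% |
| 26 / 9 | 20.6% | 36.0% / 28.0% | 15% |
| 30 / 10 | 23.5% | 38.6% / 28.3% | 21% |
| 20 / 0 | 11.8% | 32.7% / 25.0% | 16% |

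The first and last rows show that the overall fraction is the wrong trigger. Balanced loss at 20% does no harm here; one-sided loss at 11.8%, well inside the window, does. In that last row the planned imputation would run, but it would still rest on missing at random.

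**The case against.** The other side has several good points.

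- **The primary test is not stated to be complete-case.** A reader might infer that the plan drops every patient without an M3 FIQ. It does not say so, and the full protocol or analysis plan may hold another rule. Observed-case is the natural reading, because imputation is confined to the sensitivity analysis and N is inflated for loss, but it remains an inference.
- **Device intolerance need not mean missing data.** Section {11b} keeps patients who stop the wristband because of an adverse effect in follow-up. Participation ends only "In case of a serious adverse event that no longer allows the patient to participate in the study".
- **Losses may be small.** Section {18b} expects very few and lets the patient complete the FIQ remotely. Delayed patients receive the wristband at M3, which is a reason to stay. Reaching 35 missing takes about twice the planned loss.
- **Other analyses exist.** The primary outcome is re-evaluated at M6 and M9 with mixed regressions ({12}, {20a}), which may use patients with incomplete visits. They are secondary, come after M9, and in their usual form also assume missing at random.
- **Worst-case bounds prove little about the cut-off.** With observed rates of 50% and 25% and a fraction m missing in each arm, the lowest possible difference is 0.50(1 − m) − [0.25(1 − m) + m] = 0.25 − 1.25m. It reaches zero at m = 20%. A reader might infer that the rule lapses exactly where the sign becomes uncertain, but that crossing comes from the assumed rates, not from the rule. At 10% the bound is still +12.5 points.

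These points lower the chance of harm. They do not give a reason for the upper limit, define the denominator, or supply a check outside missing at random.

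**Conclusion.** The point holds as a should-fix. The 5–20% condition is explicit and removes the only stated missing-outcome analysis of the primary endpoint when it is most needed: from 35 of 170 patients, if the percentage counts patients. Its denominator is ambiguous, and no stated check departs from missing at random.

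The size depends on assumptions the article cannot settle. Under the 26 versus 9 split with all missing patients non-responders, the observed-case test rejects a true null about 15% of the time; with equal loss it stays at about 3.4%. The splits are assumed, and harm requires dropout that is both differential and related to response. At the planned 10% loss the imputation check operates.

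The documents do not support going further and making multiple imputation the primary analysis. That would replace the Fisher test with a method resting on the very assumption in question. If it drew on later FIQ values, those would be incomplete when the M3 analysis is run.

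**What to change.** - Delete the 5–20% condition. Run the multiple-imputation sensitivity analysis whatever the fraction of patients without an M3 responder status, and count that fraction in patients.
- Always report missing = non-responder for all 170 randomised patients.
- Always report a tipping-point analysis that varies the response rate of missing patients separately by arm. It is needed alongside the previous item, because missing = non-responder favours Immediate if Delayed loses more patients.
- Keep the Fisher test as primary. If it uses only patients with an M3 FIQ, describe it as observed-case.

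The cost is a little programming and a result that may look less favourable; no new data are needed. The change should be dated before the M3 database is frozen. Inclusion ended on 1 April 2022, so the last M3 visits fell around 1 July 2022, or mid-July with the two-week window. If the M3 data have already been analysed, the added analyses should still be reported, labelled as added afterwards.

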### Plans to give access to the full protocol, participant-level data and statistical code {31c}

The protocol is available on request from the sponsor. At this time, there are no plans to provide access to the participant-level data and statistical code.

## Oversight and monitoring

### Composition of the coordinating center and trial steering committee {5d}

The coordination of the trial is carried out within the sponsor’s medical team. It is composed of the company’s scientific manager, a neuropsychologist, a clinical trial coordinator, and a data manager. The neuropsychologist provides initial training of coaches and, if needed, provides guidance to coaches for their first coaching sessions and throughout the study. The trial coordinator ensures that the trial runs smoothly from both a clinical and a material point of view. The data manager ensures the quality of the data entered in the eCRF to limit the number of missing or aberrant data. This coordination team meets on a weekly basis.

In this study, there is no steering committee.

### Composition of the data monitoring committee, its role, and reporting structure {21a}

There are no data monitoring committees because the primary outcome is a self-questionnaire completed by the patient, and moreover, this study is considered by the French law like a low or negligible risk study. A data monitoring is subcontracted to the Research and Innovation Department of Grenoble Alps University Hospital. A monitor Clinical Research Assistant visit each center at least once a year to ensure that: informed consent is signed from each patient, the clinical center respects the clinical protocol, the data are complete and accurate, and the source data are present in the center.

### Adverse event reporting and harms {22}

This clinical study is considered by the French law like a low or negligible risk study. So, the vigilance of the clinical trial is identical to that of medical care. However, any adverse event is collected immediately in the eCRF and the sponsor is informed by an email alert from the eCRF. If it is an adverse effect, an analysis of the internal data of the wristband is performed to best describe this event. In case of serious adverse effects, a declaration to the health authority would be made by the sponsor.

### Frequency and plans for auditing trial conduct {23}

An audit conducted at the request of the sponsor or an inspection conducted by the health authorities may be carried out at any time by persons who are independent of those responsible for the research. The objective is to ensure the quality of the research, the validity of its results, and compliance with the law and regulations in force. The auditors/inspectors must have direct access to the source and medical data and to any useful document related to the conduct of the clinical study. The confidentiality of the data and the anonymity of the subjects will be respected. Investigators agree to comply with the requirements of the sponsor and the competent authority with respect to an audit or inspection of the research.

### Plans for communicating important protocol amendments to relevant parties (e.g., trial participants, ethical committees) {25}

In case of major modifications of the protocol, an authorization will be requested from the ethics committee. Once approved, the new protocol version will be distributed to the research teams of each center and to the structure responsible for the data monitoring.

### Dissemination plans {31a}

Trial results will be presented to the staff of the different centers involved in the study. They will also be published in a peer-reviewed journal as well as in national and international conferences. A summary of the results can be given to patients who participated on their request.

## Discussion

The aim of this multicenter, randomized, and controlled study is to demonstrate the effectiveness of the integrative approach based on endorphins stimulation and a coaching program for patient suffering from fibromyalgia. If the effectiveness of the solution is demonstrated, we will be able to respond to the demand of fibromyalgia patients for access to an effective non-medicinal treatment to improve their quality of life, and confirm the key recommendation for nociplastic pain, emitted by the EULAR: drug-free approach as first intention and multidisciplinary care [39]. The randomization is of type immediate intervention vs delayed intervention. The Delayed group is the control group that receives the solution after the evaluation of the primary endpoint at 3 months. During these first 3 months, this group receives standard care, so we compare the solution to standard care. The purpose of this methodology is to limit deception bias and facilitate inclusion.

It is recommended that patients use the wristband for a minimum of 3 sessions per day. One of the strengths of this protocol is the follow-up in real-time and for each patient of the realization of the sessions thanks to the extraction of the data from the wristband to the smartphone application. This allows the patient to know at any time of the day the number of sessions performed. This data also allows coaches to remotely monitor their patients’ compliance. In case of poor compliance, the coach can recommend to the patient to increase the frequency of use during a coaching session or by sending a notification to the patient's smartphone. This objectivized compliance with real data will allow us to carry out our per-protocol analysis with patients having completed at least 80% of days with two or more sessions per day.

One of the weaknesses of this protocol is that it is not double-blind, as most of the non-medication and multi-disciplinary clinical trial, as it is impossible to use a placebo arm. However, the primary endpoint and most of the secondary endpoints are patient self-reports.

In addition, patients are encouraged to complete their questionnaires and booklet directly on the eCRF at home, which makes these data independent of any clinician or coach judgment.

## Trial status

At the time of submission, the version of the protocol is V3.0 filed on March 11, 2022. Inclusions started on November 15, 2021, and ended on April 1, 2022. The 9-month follow-up per patient is underway. We had initially planned a 12-month period to include all 170 patients. When the start of the study was announced, the patients followed in each of the 8 centers contacted their physicians to express their wish to participate in this clinical study, and thus, the inclusions were carried out extremely quickly for a clinical trial of this size.

## Data Availability

The final database will be kept by the subcontractor who performs the statistical analyses for 15 years. A copy will be given to the sponsor who will archive it for 15 years once. No data can be reused without the agreement of the sponsor and without compliance with French regulations.

## Abbreviations

ACR: American College of Rheumatology
CGIC: Clinician Global Impression of Change
CRA: Clinical Research Assistant
DSM: Diagnostic and Statistical Manual of mental disorder
eCRF: Electronic case report form
EQ-5D-5L: Euroquol - 5 dimensions – 5 levels
EULAR: European League Against Rheumatism
FIQ: Fibromyalgia Impact Questionnaire
FM: Fibromyalgia
GPAC: Global Physical Activity
HAD: Hospital and Anxiety Depression
meCUE: Modular evaluation of key Components of User Experience
MFI: Multidimensional Fatigue Inventory
MMW: Millimeter waves
PGIC: Patient Global Impression of Change
PSQI: Pittsburg Sleep Quality Index
QoL: Quality of life
TPE: Therapeutic Patient Education
VAS: Visual analogic scale
